### Upper body functionality

The disability of the arm, shoulder and hand (DASH) questionnaire: the American Academy of Orthopedic Surgeons introduced the DASH questionnaire as a specific instrument to measure upper extremity functionality [49]. It is one of the most extensively used tools [50]. Of the 30-items that are included in the DASH questionnaire: 21 items ask about the degree of difficulty in physical activities; 5 items ask about the severity of some pain symptoms; and the final 4 items ask about other activities such as social activities, sleep, work or self-image. The impact of the symptoms on each activity is also assessed. The scale score ranges from 0 to 100 points; the higher the score, the greater the disability [51]. The reliability of the Spanish version has a Cronbach’s α = 0.96 [52].

### Active range of motion (AROM)

Shoulder AROM measurements will be obtained using a standard, two-armed goniometer, which is described as the clinical gold standard [53]. The patients will be asked to actively move their arms as much as they can to obtain measurements (in degrees) of flexion, extension, abduction, internal rotation and external rotation of the shoulder [23]. The movement will be validated by the interviewer and motion compensation will be limited to avoid overestimating the scores.

### Cognitive function

Wechsler Adult Intelligence Scale (WAIS-IV): The WAIS-IV is an intelligence test designed to measure cognitive ability in adults and older adolescents and provides the most advanced adult measure of cognitive ability [54]. WAIS-IV subtests will be administered and scored according to standardized procedures [55]. For feasibility issues and because specific subtests provide information on a specific cognitive function (and can be used separately [55]), we will use two of the four index scores that compose the test: the Working Memory Index (WMI) and the Processing Speed Index (PSI). The WMI includes two subtests, Arithmetic and Digit Span, and the PSI also includes two subtests, Digit Symbol-Coding and Symbol Search.

The Trail Making Test (TMT) measures the flexibility of thinking using a visual-motor sequencing task and is one of the most important neuropsychological tests, providing information on speed of processing, visual search, mental flexibility, scanning and executive functions [56]. It is formed by two subtests. TMT-A requires the participant to draw lines that sequentially connect several encircled numbers (1 to 25) distributed on a sheet of paper. TMT-B is similar in requirements, but in this case, the participant must alternate between numbers and letters (e.g., 1, A, 2, B, 3, C, etc.). The score is based on the amount of time required to complete the task.

### Anxiety and depression

The Hospital Anxiety and Depression Scale (HADS): This scale consists of 14 items with two subscales (seven items for anxiety and seven for depression) and a score which ranges from 0 to 21 for each subscale. The questionnaire contemplates a cutoff point of 11 or above to consider anxiety and depression conditions [57, 58].

### Physical fitness

Short Version of the Minnesota Leisure Time Physical Activity Questionnaire (VREM) [59]: This questionnaire is a short version of the original Minnesota questionnaire [60] and is composed of 5 items. It asks for the period in a typical week that the participants perform routine housework activities (cleaning house and go shopping on foot). In addition, it asks about activities performed during the last month or in a typical month for the other items, such as walking, working in the garden, playing sports or dancing and climbing stairs. Finally, energy expenditure is calculated (in METS-min/14 days) and the participant is classified from sedentary to very active according to their energy expenditure [59].

Self-Efficacy Scale for Physical Activity (EAF): The EAF is a validated instrument that determines the participants’ beliefs about their own abilities to perform physical activities (self-efficacy for physical activity). It also allows us to identify the barriers and limitations that prevent the user from practicing this behaviour and the strength they require to perform regular physical activity. The EAF consists of three domains: scheduled physical exercise, physical activity in daily activities and walking. A total of 39 items are rated from 0 to 10; the higher the score, the greater the ability to perform the activity [61, 62].

### Accelerometry

Accelerometry will be used to obtain data about physical activity and sedentary time for each participant, following a previously published protocol for usage and analysis [63]. A pre-programmed tri-axial accelerometer (ActiGraph GT3X+, Pensacola, Fl., US) and a daily questionnaire will be given to BCS. The participants will wear the accelerometer for 8 consecutive days. They will be instructed to wear the accelerometer on their lower back for the whole day (including when sleeping) but to take it off during aquatic activities. They will also receive an information sheet with detailed instructions. Participants will be included in the main analysis if the device records data for at least 4 days over a period of at least 10 h each day. Data will be collected at intervals of 1 min. Nonwear periods (intervals of 60 consecutive minutes with zero counts) and the first day of wearing the device will be excluded from analyses. Accelerometer data will be downloaded to the same computer used to initialize them [18].

### Lymphedema

We will measure changes in size or volume of the upper limbs to diagnose lymphedema. An inextensible flexible tape 0.5 cm wide x 2 m long with an accuracy of 0.1 cm will be used following the protocol using in some previous studies [18, 64], which has been shown to be valid and reliable [65, 66].

### Sample size

The sample size and power calculations for this trial were obtained through overall Health-Related QoL (HRQoL) using EORTC QLQ-C30 version 3.0 [40], and taking into account previously reported data [67] a minimally important difference from 5 to 10 points was considered. Assuming that integral group increase HRQoL in BCS in compared with m-health group [18] we can detect differences of at least 5% with a power of 90% and an α of 0.05 with two groups (Integral group and m-health group) of 36 participants assuming similar standard deviation (approximately 7 points). A maximum loss at follow-up of 10% will be allowed to face a possible drop-out rate [9]. Hence, we will recruit 80 BCS (40 in each group). Fig. 1 shows the flow diagram of the study participants.

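### The stated 90% power is not supported for a two-sided 0.05 test: 36 women per group give about 85% for a 5-point difference with SD 7

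*Protocol article*

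**What the plan says.** All the inputs stand in one paragraph of the protocol article, under Sample size. It works with overall health-related quality of life on the QLQ-C30 and says that "a minimally important difference from 5 to 10 points was considered". It gives a direction, "Assuming that integral group increase HRQoL in BCS in compared with m-health group", and then the claim: "we can detect differences of at least 5% with a power of 90% and an α of 0.05 with two groups", followed by "of 36 participants assuming similar standard deviation (approximately 7 points". For attrition, "A maximum loss at follow-up of 10% will be allowed", which leads to 40 per group and 80 in all.

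The paragraph does not say whether alpha is one-sided or two-sided, names no test, and does not say what the 5% is a percentage of. Under Primary outcome measure, the article says that the QLQ-C30 scores run from 0 to 100. Under Data analysis, the main analysis is a repeated-measures ANCOVA adjusted for age, surgery type, tumour stage and time from diagnosis; baseline quality of life is not in that list.

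**The concern.** Difference, SD, alpha, power and group size are all printed, so they can be checked against each other. Under a conventional two-sided 0.05 test they do not agree: 36 per group falls short of 90% power for 5 points with SD 7.

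This is the power statement for the primary outcome. At the lower end of the trial's own range for a minimally important difference, the type II error would be about 15% rather than 10%. A non-significant result would then be read with more confidence than the design gives. Stating the target as a percentage, beside a minimally important difference and an SD in points, adds a second ambiguity to the same sentence.

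**Working it through.** **Inputs (Sample size section).** Difference 5 points, the lower end of the stated range; SD 7; alpha 0.05; 36 per group; stated power 90%; 10% loss.

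**Formulas.** Two equal groups, normal approximation:

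- n per group = 2 × (z_alpha + z_power)² × SD² / difference²
- power = Φ(difference / (SD × √(2/n)) − z_alpha)

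Each result was checked with the noncentral t distribution, marked t below; z marks the normal approximation.

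**1. Can the plan's own figures be reproduced?**

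- Attrition: 36 / (1 − 0.10) = 40. This agrees exactly.
- One-sided alpha 0.05: standard error = 7 × √(2/36) = 1.650, and 5 / 1.650 = 3.030. Power = Φ(3.030 − 1.645) = 91.7% (t: 91.2%). For 90% the formula asks for 34 per group (t: 35). This is close to the plan's 36 and 90%.
- Two-sided alpha 0.05 with SD 6.5: standard error = 1.532, and 5 / 1.532 = 3.264. Power = Φ(3.264 − 1.960) = 90.4% (t: 89.6%), and n = 36 (z).

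**2. Two-sided alpha 0.05 with the printed SD of 7.**

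- Power at 36: Φ(3.030 − 1.960) = Φ(1.070) = 85.8% (t: 84.8%).
- Power at 40, with nobody lost: 5 / (7 × √(2/40)) = 3.194, so Φ(1.234) = 89.1% (t: 88.4%).
- n for 90%: 2 × (1.960 + 1.282)² × 49 / 25 = 41.2, so 42 per group (t: 42.2, so 43).
- n for 85%: 2 × (1.960 + 1.036)² × 49 / 25 = 35.2, so 36 per group. By this formula, the printed group size is the one for 85% power.
- Difference detectable with 90% power at 36: 1.650 × (1.960 + 1.282) = 5.35 points (t: 5.42).

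**3. Sensitivity to an SD given only approximately** (two-sided, 36 per group, 5 points).

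| SD | Power, z | Power, t |
|---|---|---|
| 6.5 | 90.4% | 89.6% |
| 7.0 | 85.8% | 84.8% |
| 7.5 | 80.7% | 79.7% |

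Over the values that round to 7, power runs from about 80% to about 90%. The printed figure is at the favourable end.

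**4. Could adjustment for baseline give 90%?** With a baseline-outcome correlation r, the residual SD is 7 × √(1 − r²). At r = 0.4 it is 7 × √0.84 = 6.42, and power at 36 per group is 91.1% (t: 90.3%). At r = 0.35 it is 89.9% (z). A correlation of about 0.4 would therefore be enough, but the Sample size section assumes none.

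**The case against.** The best defence is that two-sidedness is the reader's assumption, not the plan's. The section gives alpha without a side, words its hypothesis directionally, and the trial is a superiority design. One-sided at 0.05, the claim is met. The SD is also only approximate, and 6.5 returns 36 per group even with a two-sided test. Both points stand, and they limit the claim: the documents do not support saying that 90% is wrong under every reading. A reader might also infer that no level of retention could reach 90%. That holds only for a two-sided test with SD 7; at 40 per group a one-sided test with SD 7 has 93.6%.

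These points do not rescue the sentence as printed. No one-sided test is declared anywhere, an unqualified 0.05 is conventionally two-sided, and the usual F test of the planned ANCOVA has no direction. Rounding of the SD works both ways, and 7.5 gives about 80%. The covariates or the repeated measurements might add precision, but the section claims no such gain.

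A second inference to resist is that the percentage means a smaller, relative target, such as 5% of a group mean. The article gives no mean to apply it to, and on a 0 to 100 scale 5% of the range is 5 points, which matches the lower end of the range just before it. It is a loose unit, not evidence of a different target. Likewise, nothing in the article supports replacing the SD with a much larger one.

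Finally, the shortfall applies at the lowest edge of the 5 to 10 point range. From about 5.4 points upward, two-sided power is at least 90% with SD 7. That is correct, but the sentence makes its claim for differences from 5 upward.

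**Conclusion.** Wrong as written, under the conventional reading. For a two-sided 0.05 comparison of two means with a 5-point difference and SD 7, 36 per group give about 85% power (84.8% t, 85.8% z), not 90%. The type II error is about 15% against the 10% implied.

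The conclusion depends on two things the section leaves open: the side of the test and the exact SD. The gap of about 5 percentage points closes with a one-sided alpha or an SD near 6.5, and roughly doubles at SD 7.5. The design remains usable; its power is overstated for the smallest difference that it names.

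**What to change.** Keep 80 women and correct the sentence. Suggested text: *With 36 women per group, a two-sided test at the 0.05 level has about 85% power to detect a difference of 5 points in overall QLQ-C30 quality of life, assuming a standard deviation of 7 points; power is 90% for a difference of about 5.4 points.* Give the target in points and name the test.

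If the 90% is to stay, declare the assumption that yields it:

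- a one-sided alpha of 0.05;
- the exact SD and its source, if it is nearer 6.5; or
- a baseline-adjusted analysis with an assumed baseline-outcome correlation of about 0.4. Baseline quality of life is not among the covariates listed under Data analysis, so this option also means changing or clarifying the analysis model.

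Restating the power is a change of wording only and needs no extra patients; the stated power becomes slightly less favourable. For comparison, reaching 90% two-sided by recruitment would need 42 / 0.9 = 46.7 to 43 / 0.9 = 47.8 per group, that is 47 to 48 per group or 94 to 96 women.

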**Fig. 1 Fig1:**
[figure not shown]
Flow diagram showing the recruitment of patients

### Randomization and blinding

To reduce the risk of bias during the assessment, after completion of the baseline assessment we will allocate eligible patients randomly either m-health or integral groups into three randomization waves, using computer-generated numbers (EPIDAT 3.1, Xunta de Galicia). An external member will introduce the sequence in sealed opaque envelopes. Assessment staff will be blinded to patients’ randomization assignment and the staff responsible of the rehabilitation program will not be able to change any assignment. After the 6-month follow-up period, and because of ethical implications, once the last outcome variable has been measured we will invite participants of the m-health group to participate into the face-to-face rehabilitation program.

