### Participants

A total of 80 eligible (see inclusion criteria below) BCS will be randomized into the integral group (*N* = 40) or the m-health group (*N* = 40). For feasibility, the study is conducted in three waves. During the first year of the study (from January to December 2016), we will prepare protocols, establish the measurement techniques, and enrol the first 25 women in the study. At the beginning of the second year of the study (between January and April 2017), we will enrol an additional 30 women, and in the third stage, we will enrol the remaining 25 women. In summary, the target sample size of 80 BCS will be achieved in these 3 waves.

The integral group will receive the m-health plus an 8-week occupational therapy onsite program, and the m-health group will only use the app. Participants will be enrolled in this study by oncologists from the Hospital Virgen de las Nieves (Breast Unit) and the Hospital Clínico San Cecilio, Granada (Spain). The Research Ethics Committee of the province of Granada approved this study.

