### Data analysis

All analyses will be carried out using STATA/SE 14.0 StataCorp, College Station, TX, USA) or using Statistical Program for Social Sciences (IBM© SPSS© Statistic version 20, Corp., Armonk, NY). We will check the normal distribution of variables with Kolmogorov-Smirnov and Shapiro-Wilk test, as appropriate, and the differences at baseline between groups with Chi-square test or Student *t*-test, as appropriate. The main analysis will be repeated measures analyses of the covariance (ANCOVA) with age, type of surgery, tumour stage and time since diagnosis as covariates. Intergroup effect sizes will be calculated to provide change magnitude information. We will use the intention-to-treat principle for all analyses.

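### Women are randomised in three calendar-time waves, but wave is missing from the main model's named covariates: a minor loss of precision, not a bias

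*Protocol article*

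**What the plan says.** Under Randomization and blinding, the protocol article states that "we will allocate eligible patients randomly either m-health or integral groups into three randomization waves", "using computer-generated numbers (EPIDAT 3.1, Xunta de Galicia").

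Under Participants, it gives the reason and the sizes. The reason is practical: "For feasibility, the study is conducted in three waves". In 2016 the team will "enrol the first 25 women in the study"; between January and April 2017 "we will enrol an additional 30 women"; in a third, undated stage "we will enrol the remaining 25 women". The total is 25 + 30 + 25 = 80, with 40 per group overall.

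Under Data analysis, the main model is a repeated measures ANCOVA "with age, type of surgery, tumour stage and time since diagnosis as covariates". Wave is not on that list. The article does not say whether allocation is blocked, stratified or otherwise held near 1:1 within a wave.

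**The concern.** The article gives a named covariate list, so the omission of wave is a stated choice. Wave is the one grouping by which the randomisation is described as being organised, and it is the one that the model ignores.

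Waves recruited at different times could differ in outcome level or in change, for example through season (physical activity is among the measures) or through growing staff experience with a newly developed programme. The document asserts no such differences; they are only plausible. If they exist and allocation is balanced within wave, the model's error term contains variance that the design has already removed from the group comparison. At stake is some precision in a trial of 80 women.

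**Working it through.** **Inputs.** From Sample size: a difference of 5 ("we can detect differences of at least 5" per cent, read here as 5 points on the 0-100 scale), SD about 7, power 90%, alpha 0.05, 36 per group, 10% loss. From Participants: waves of 25, 30 and 25. Assumption, not in the documents: wave explains a share R² of outcome variance, set at 0% to 20%.

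**The plan's own figure.** n per group = 2 × (z_alpha + z_power)² × SD² / difference².
- Two-sided: 2 × (1.960 + 1.282)² × 49/25 = 41.2, so 42. With the noncentral t, power at 36 per group is 84.8%.
- One-sided: 2 × (1.645 + 1.282)² × 49/25 = 33.6, so 34, within 2 of the stated 36.
- Loss: 36/0.90 = 40 per group, 80 in total, which reproduces.

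None of these figures depends on wave. Sidedness is a separate matter; two-sided tests are used below.

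**Formula check, allocation balanced within wave.** The model without wave estimates the standard error from the full SD. The true standard error depends only on the within-wave SD, 7 × √(1 − R²). The ratio of reported to true standard error is therefore 1/√(1 − R²).

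| R² (assumed) | SE ratio | Within-wave SD | Power at 36 per group with that SD | Difference from 84.8% |
|---|---|---|---|---|
| 0% | 1.0000 | 7.00 | 84.8% | 0 |
| 5% | 1.0260 | 6.82 | 86.6% | 1.8 points |
| 10% | 1.0541 | 6.64 | 88.3% | 3.5 points |
| 15% | 1.0847 | 6.45 | 90.0% | 5.2 points |

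For balanced waves the last column is an upper figure. It ignores that balance already reduces the true sampling error of the unadjusted estimate.

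**Simulation, allocation balanced within wave.** N = 80, one post-baseline endpoint, total SD 7, true difference 0 or 5, no other covariates; 8,000 runs per row, and 20,000 for the 15% row.

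| R² | Model SE, wave omitted | True SE | Ratio | Type I error, wave omitted | Power, wave omitted to included |
|---|---|---|---|---|---|
| 0% | 1.557 | 1.550 | 1.005 | 5.1% | 88.5% to 88.5% |
| 5% | 1.562 | 1.545 | 1.011 | 4.5% | 88.8% to 89.6% |
| 10% | 1.563 | 1.493 | 1.047 | 3.9% | 89.8% to 91.6% |
| 15% | 1.561 | 1.434 | 1.089 | 3.3% | 90.5% to 93.0% |
| 20% | 1.568 | 1.388 | 1.130 | 2.7% | 91.0% to 94.6% |

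The Monte Carlo error of a true SE from 8,000 runs is about 1/√16,000 = 0.8%, so 1.011 and the formula's 1.026 at a 5% share are compatible. With wave included, type I error is about 5% in every row.

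**Simulation, allocation not restricted within wave.** With wave omitted, type I error is 4.9-5.3% and there is no bias beyond simulation error. With only the 40/40 total fixed, including wave moves power from 88.7% to 87.8% when wave has no effect, from 88.6% to 90.9% at a 10% share, and from 88.5% to 93.7% at 20%. Under simple randomisation with no wave effect it moves from 87.8% to 86.7%.

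**The case against.** The case for leaving the model alone is substantial.

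- **Wave is not declared a stratification factor.** The waves are there for feasibility, and no within-wave restriction is stated. This stands. It is why the effect on standard errors can only be stated conditionally.
- **The size rests on an assumption.** No between-wave variance is given. At a share of 0-1% nothing is gained, and with unrestricted allocation adjustment can cost about 1 point of power. This stands. Wave is also a rough proxy for season, since the first stage covers a full year and the third is undated.
- **The repeated measures model may absorb part of it.** If the group comparison rests on change over time, a constant wave difference in level cancels within each woman, and only wave differences in change matter. This stands. The single-endpoint figures above may therefore overstate the gain.

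Stronger readings are tempting, but the document does not support them. A reader might infer that omitting wave harms balance; balance is set by the allocation, and no analysis model can worsen it. A reader might infer confounding; under random allocation any wave imbalance is due to chance, the ordinary standard error covers it, and expected bias is zero. A reader might compute that the arms in a 25-woman wave differ by 5 or more in 42% of cases (binomial). That ignores the fixed 40/40 total, which gives 33% (hypergeometric), and such differences do not threaten validity. Finally, 25 being odd is not a defect: a 13/12 split is ordinary, and 40/40 overall does not require equal arms in each wave.

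What remains is that the article describes randomisation by wave, fixes its covariates by name and omits wave.

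**Conclusion.** The point holds as a minor precision improvement. If allocation is balanced within wave, the stated model gives standard errors that are too wide and a conservative test: by about 1-3% at an assumed 5% wave share, 5% at 10% and 8% at 15%, and not at all if wave has no effect. The power gain from adjustment is about 1-2 points at 5% and 2-4 at 10%. At 15% the formula gives 5 points and the balanced simulation 2.5, so 5 is best read as an upper figure. If allocation is unrestricted within wave, the stated analysis is valid and unbiased and merely less precise than it could be. In neither case is there false-positive inflation. The omission itself is certain from the text; its size depends on a wave variance and a within-wave restriction that the document does not give.

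**What to change.** Add wave as a three-level fixed factor to the primary and secondary models under Data analysis. If the group comparison is a contrast over time, let wave vary by visit as well, so that wave differences in change are also removed. State this before any outcome comparison, so that adjusting for wave is not a later choice. One sentence on whether allocation is restricted within wave would make the basis for the adjustment clear.

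The cost is a line of text and 2 degrees of freedom (2 per time contrast if wave varies by visit), and at most about 1 point of power if wave has no effect and allocation is unrestricted. The sample size and the conduct of the trial do not change.
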